### Ethical considerations

The study will be conducted in accordance with the ethical standards established in the 1961 Declaration of Helsinki (as revised in Hong Kong in 1989 and Edinburgh, Scotland, in 2000) and is in compliance with the Regulatory Guidelines and Norms for Research Involving Human Subjects of the National Health Board of the Brazilian Health Ministry issued in October 1996. This protocol received approval from the Human Research Ethics Committee of Universidade Nove de Julho (Brazil) under process no. 368856/2010 and is registered with the World Health Organization under Universal Trial Number (UTN) U1111-1127-9390 and the Brazilian Registry of Clinical Trials (REBEC no. RBR-7YHR4W). All participants will be required to sign a statement of informed consent and will be allowed to withdraw from the study at any time with no negative consequences. All the procedures of the study will be confidential.

### Evaluation protocol

#### Clinical evaluation

Patients with chronic kidney diseases and end-stage renal disease undergoing dialysis, based on recommended procedures, will be submitted to general physical measurements performed by a well-trained physician and physical therapist before and after the dialysis session using precise instruments. The measurement protocol will include body weight (kg); height (cm); body mass index (BMI) calculated using the formula weight/height^2^[16]; circumferences (cm) of the neck, waist, and hip [20]; heart and respiratory rates; blood pressures; Mallampati index [21]; tonsil index [22]; heart rate variability [23]; maximum ventilatory pressure; negative expiratory pressure (NEP) test; and polysomnography (PSG; sleep study), as well as the administration of specific questionnaires addressing sleep apnea, excessive daytime sleepiness [24,25], symptoms of stress [12], and depression [12-14], anxiety [15], and quality of life [26,27].

The following data will be obtained from medical charts: biochemical values, associated pathological conditions, laboratory values (iron, intact-parathyroid hormone, haemoglobin, calcium, phosphorus, and creatinine), duration of dialysis therapy, comorbidities, and aetiology of kidney disease.

#### Physical examination

Weight and height determinations will be performed using an electronic scale (model 200/5; Welmy Industria e Comercio Ltda, São Paulo, Brazil), and the BMI will be calculated [16]. For the assessment of the tonsils and Mallampati index scoring, each subject will be in the sitting position and instructed to open the mouth as wide as possible [21,22].

#### Waist and neck circumferences

Measurements of waist and neck circumferences will be performed with a metric tape (7 mm in width). The sites for the measurements will be standardised. Waist circumference will be measured at the midpoint between the lower edge of the last rib and the iliac crest. Neck circumference will be measured horizontally over the cricoid cartilage [28].

#### Thorax and abdomen cirtometry

Cervical-thoracic abdominal cirtometry will be performed to assess thorax and abdomen mobility and define the diaphragm index. The measurement will be performed by fixing the zero point on the metric tape to the anterior region of the thorax at the level that is being measured (axillary, xiphoid, or abdominal), with the tape encircling the entire circumference of the thorax or abdomen with maximal possible pressure and the other extremity of the tape placed over the same fixed point. The aim of applying the maximal possible pressure of the tape on the body is to avoid the interference of soft structures in the measurements. Mobility and range of motion will be provided by maximal inspiration and expiration [29].

### Lung function tests

#### Spirometry

Lung function tests will be performed during the day, with the patient seated in a comfortable position. For such, the KoKo PFT Spirometer System version 4.11 (nSpire Health, Inc, Louisville, CO, USA) will be used in accordance with the guidelines for the execution of lung function tests established by the Brazilian Society of Pneumology [30] and European Respiratory Society [31]. The subjects will perform the test in a comfortable position, with the body erect and upper limbs unsupported. All the examinations will be performed by a competent technician trained in obtaining the necessary cooperation from the subjects and appropriately operating the equipment to ensure accurate, reproducible results. The spirometer will be calibrated before each exam using a 3-L syringe [30].

#### Analysis of respiratory mechanics

Maximal inspiratory pressure and maximal expiratory pressure physiologically constitute the most adequate test for the determination of ventilatory muscle strength. Maximal inspiratory pressure is an indicator of ventilatory capacity and the development of respiratory failure, the measurement of which is indicated for the assessment of the degree of abnormality and monitoring of the weakening of individual inspiratory muscles in disease progression [32]. The tests will be performed on the same day on which the patients will undergo spirometry. The tests will be performed in a quiet setting. The patients will be seated comfortably, breathing calmly and at rest, with the trunk at a 90-degree angle in relation to the thighs [30].

### Sleep evaluation

#### Berlin questionnaire

The Berlin questionnaire is used to identify patients at high risk of respiratory sleep disorders in a variety of populations. This clinical history questionnaire has recognised efficacy in distinguishing individuals at high risk of OSA, with 10 items organised into 3 categories as follows: snoring and apnea (5 items), daytime sleepiness (4 items), and systemic arterial hypertension and obesity (1 item). All marked responses are considered positive. The score is divided into the following categories: category 1 is considered positive in the occurrence of 2 or more positive responses to items 1 to 5; category 2, in the occurrence of 2 or more positive responses to items 6 to 8; and category 3, when the response to item 9 is “yes” or when the BMI ≥ 30 kg/m^2^. Two or more positive categories indicate a high risk of OSA [24].

#### Epworth Sleepiness Scale

The Epworth Sleepiness Scale is a simple, self-administered questionnaire with items addressing situations involving activities of daily living and the occurrence of daytime sleepiness in adults. The subjects will be instructed to classify their likelihood of feeling the desire to nap or sleep in 8 situations on a scale of 0 to 3 (0, no chance of napping; 1, small chance of napping; 2, moderate chance of napping; and 3, strong chance of napping) [25,33].

#### Polysomnography

All the patients will undergo a standard overnight PSG (Embla, A10 version 3.1.2 Flaga, Hs. Medical Devices, Reykjavik, Iceland) at the Sleep Laboratory of Nove de Julho University*.* Polysomnography exams will be held the night before the haemodialysis and approximately 12 hours after this dialysis. All recording sensors will be attached to the patient in a non-invasive manner using tape or elastic bands. The following physiological variables will be monitored simultaneously and continuously: 4 channels for the electroencephalogram (C3-A2, C4-A1, O1-A2, and O2-A1), 2 channels for the electrooculogram (EOG-Left-A2 and EOG-Right-A1), 4 channels for the surface electromyogram (muscles of the submentonian region, anterior tibialis muscle, masseter region, and seventh intercostal space), electrocardiogram (derivation V1 modified), airflow detection via 2 channels through a thermocouple and nasal pressure cannula, respiratory effort of the thorax and abdomen via x-trace belts, snoring and body position sensors, and arterial oxygen saturation and pulse rate via an oximeter.

All the subjects will be monitored by a technician experienced in PSG. Sleep stages will be visually scored in 30-s epochs, and each PSG recording will be analysed manually under blinded conditions by the same examiner with experience in scoring PSG recordings in accordance with international standards established by the Academy of Sleep Medicine Manual for Scoring Sleep and Associated Events. The patients will be instructed to remain as relaxed as possible and sleep naturally, as if at home. All signals will be recorded continuously [34,35].

#### NEP test

The NEP test will be conducted before and after hemodialysis sessions, performed through the administration of a negative pressure at the mouth during expiration. This is a practical test performed while awake and requires little cooperation from the subject. In the absence of expiratory flow limitation, the increase in the 8 pressure gradients between the alveoli and the open upper airway caused by NEP results in an increase in expiratory flow.

NEP will be generated by the Super Air Amplifier (Exair model 120021, Cincinnati, OH, USA) coupled to a tank of compressed air via an electrically operated solenoid valve (model 95004, Norgren Ltd; Vimercate, MI, Italy) automatically activated in early expiration and kept open for 2 s by software control (Figure 2). A pneumotachograph (Hans Rudolph model 3830; Kansas, MO, USA) will be connected to the air amplifier and the mouthpiece to measure airflow ($\dot{V}$) with pressure transducers (PCLA02X5; Sensortechnics GmbH, Puchheim, Germany). Mouth pressure will be measured by pressure transducers (PCLA0050; Sensortechnics GmbH, Puchheim, Germany). NEP of 10-cm H_2_O will be set by occluding the pneumotachograph with a stopper and adjusting the flow of compressed air-to-air amplifier (Figure 2).

**Figure 2 F2:**
[figure not shown]
Schematic representation of the negative expiratory pressure.

Each NEP manoeuvre will be performed each after at least 4 breaths to normalise the breathing pattern. The tests will be performed once with the subject seated comfortably and again in supine position on a cot. In both positions, care will be taken to maintain the comfort of the subjects, with the neck in a neutral position, as it has been documented that the position of the head exerts an influence on upper airway collapsibility [36].

All manoeuvres will be performed with the subjects awake and wearing a nose clip. The airflow and mouth pressure signals will be low-pass filtered and sampled at 200 Hz. Both digital signals will be displayed in real time on the monitor and stored on the computer for subsequent analysis. Signal analysis and solenoid valve control will be performed using software written in 9 LabVIEW 8.2 (National Instruments) developed by the Italian National Research Council, Institute of Biomedicine and Molecular Immunology “A. Monroy.”

NEP application during tidal expiration produces an immediate peak flow followed by a sudden drop of a variable degree. Upper airway collapsibility is to be evaluated by measuring flow limitation as flow drop ($\Delta \dot{V}$) expressed as the percentage of peak flow immediately after NEP administration. To avoid reflex and voluntary reactions to the NEP stimulus, the minimum flow will be identified in the first 200 ms of NEP administration [37].

Upper airway collapsibility will also evaluated by measuring V0.2 immediately after NEP administration. These values will be expressed as the percentage of mean inspiratory volume of the 3 breaths preceding NEP administration. Measured volumes will be accepted only when differences between inspiration and expiration for each of the 3 previous breaths are less than 10%. Values of V_0.2_ and $\Delta \dot{V}$ (%) are calculated as the mean of 4 measurements. Measurements of upper airway collapsibility will be evaluated as expiratory volume in 0.2 s (percentage of the mean inspiratory volume of the 3 breaths preceding NEP application) and as flow drop ($\Delta \dot{V}$), expressed as the percentage of peak flow.

### Assessment of ANS

Nerve-Express is a fully automatic, non-invasive computer-based system designed for the quantitative assessment of the ANS on the basis of the analysis of heart rate variability. This system is based on a method of clusterisation of the relationship between sympathetic and parasympathetic nervous system statuses.

This technological breakthrough is achieved by using proprietary algorithms and a new approach based on a leading theory of artificial intelligence, the Marvin Minsky’s Frame Theory. Nerve-Express provides an objective and reliable real-time evaluation of the ANS state during the orthostatic test and Valsalva manoeuvre combined with deep breathing.

A signal sensor is attached to the thorax by an elastic strap and is coupled to the Nerve-Express software program, which collects and stores the data. The modality of the exam is the orthostatic test, in which the patient goes from the supine to the orthostatic position [38,39].

### Inventory of symptoms of stress for adults

The Inventory of Symptoms of Stress for Adults (LIPP) is based on a 4-phase model of stress and its manifestations in the somatic and cognitive domains. In the initial stress phase, which is called the alert phase, the body makes greater efforts to prepare itself to cope with a stressor. This phase is considered a positive phase of stress because it is important for adjustments to environmental demands.

The second phase is called resistance and occurs when a chronic stressor demands coping for a long period of time. This phase is associated with fatigue, perception of burnout, and cognitive loss. The next phases, referred to as almost exhaustion and exhaustion, are consequences of the breakdown of resistance and loss of capacity for adjustment. During these phases, one can observe important changes in sleep, work, and libido in addition to symptoms of anxiety and depression [12].

### Hamilton anxiety rating scale (HAM-A)

The term depression is used to describe a clinical syndrome, where there are several particular signs and symptoms. Depression can occur as a primary manifestation of mood, associated with systemic medical illnesses, other psychiatric disorders or disorders arising from the use of psychoactive substances. With regard to the study of depression, has not, to date, the biological or physiological parameters to evaluate its clinical manifestations in a definitive or conclusive. So the depression scales emerge as useful tools for assessing the severity of depressive, serving to translate clinical phenomenon in objective and quantitative information. In addition to characterizing the intensity of depression, these scales would serve to evaluate the response to treatment when applied before, during and after therapeutic intervention.

Within this context, the rating scales of depression severity, whose first date from the end of the last century can be divided into ranges: a) self-assessment, b) hetero c) mixed, involving self and observer.[15]

The first scale of hetero-evaluation, that is, applied by an observer, was the Hamilton Rating Scale for Depression (HAM-D), designed and developed by Hamilton in the late 50s. Currently, it is the most widely used depression scale worldwide and is probably the most important being regarded as “standard gold” in assessing the severity of depression compared with new and used rating scales in order to check the reliability of these.

Rating Scale Hamilton Anxiety is one of the most atualemnte used to assess anxiety in patients and is composed of 14 items (6 items - Humor anxious and 8 items - Physical symptoms) that pertain to the observed behavior. The patient will respond from their own experience the classification of symptoms present in Likert scale where 0 = absent, 1 = mild, 2 = medium intensity, 3 = 4 = strong intensity and moderate intensity.

The total score reflects the general state of the patient’s anxiety, the aspects considered by the scale for the assessment are: mood, cognition, behavior, alertness and somatic symptoms, and in addition to other symptoms, scores between 0 and 17 are considered normal, between 18:25 26 moderate and 30 severe, over 30 are uncommon, but show a severe state of anxiety [40,41].

### Beck depression inventory

The Beck Depression Inventory (BDI) has 21 items, including attitude, depressive symptoms, and suicidal ideation, scored on a scale ranging from 0 to 3. The cut-off scores are as follows: <11, minimal depression; 12 to 19, mild to moderate depression; 20 to 35, moderate depression; and 36 to 63, severe depression [12].

### Quality of life

Patients with CKD may develop eating disorders due to the diet and water intake restrictions during treatment, which may also result in dysfunctional behaviour and treatment noncompliance. Thus, stress, anxiety, and depression are common among such patients and imply a reduction in quality of life. The Short Form 36 (SF-36) will be used for the assessment of quality of life. This measure has 36 questions grouped into 8 domains or scales of physical functioning, role limitations due to physical health, bodily pain, general health perception, social functioning, and role limitations due to emotional problems, vitality, and mental health [26,27].

### Study interventions

#### Haemodialysis

Regular daytime or nocturnal haemodialysis was standardised during the trial. It was performed 3 times per week, with a 4-h session duration, 250-mL/min blood flow, and 500-mL/min dialysate flow, using bicarbonate-buffered dialysate with 1.25 mmol/L ionised calcium concentration, dialysate temperature of 36.5°C, and Polyflux 17-L dialyser [42].

The ultrafiltration amount for each haemodialysis session was decided by individual dry weight, which was fixed during the trial. In addition, during the trial, the patients were not permitted to change their medication or start new drugs, especially antiplatelet agents, angiotensin-converting enzyme inhibitors, angiotensin II receptor antagonists, calcium-channel blockers, and β-blockers.

The patients who required a change in medication for medical reasons were subsequently excluded from the study. Use of *N*-acetylcysteine was also prohibited in view of its potential influence on ischemia-reperfusion injury.

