### Aims and hypotheses

The present study involving patients with CKD was designed with 4 main objectives: (1) to assess the effects of dialysis on sleep parameters and determine the prevalence and severity of sleep disorders; (2) to determine the behaviour of sympathetic and parasympathetic autonomic nervous system activity through an analysis of heart rate variability; (3) to detect upper airway collapsibility as a risk indicator for OSA; and (4) to evaluate levels of depression, anxiety, stress and quality of life. Our hypothesis is that the weather weight gain due to volume overload observed during interdialytic period will influence the degree of collapsibility of the upper airway due to narrowing and predispose to upper airway occlusion during sleep, and to investigate the effects of nocturnal hemodialysis compared to daytime hemodialysis and the influences in the physiological variables of sleep, autonomic nervous system (ANS), and respiratory mechanics and thereby compromise the quality of life in chronic kidney diseases and end-stage renal disease patients undergoing dialysis.

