### Subjects

The participants will be recruited from the Centro de Nefrologia Zona Norte (São Paulo, Brazil) and sent to the Sleep Laboratory of the Universidade Nove de Julho (São Paulo, Brazil). Patients will be recruited consecutively and screened for eligibility using a standardised protocol. The following will be used as the inclusion criteria: male or female patients aged 18 to 80 years; chronic kidney failure; candidate for kidney transplant with indication for dialysis; cognitive level sufficient for understanding the procedures and following the instructions; and agreement to participate by signing a statement of informed consent. Meanwhile, the following will used as the exclusion criteria: craniofacial abnormalities; undergoing active treatment of sleep apnea; active malignancy; active alcohol and/or drug abuse; and dementia or treatment-refractory psychiatric diseases leading to an inability to provide informed consent.

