### Sample size calculation and statistical analysis

According to the findings of a previously published epidemiological study [17] that the proportion of adults with an apnea/hypopnoea index (AHI) ≥ 15 corresponds to 16.9% of the Brazilian population and that of a previous study [18] that AHI ≥ 15 had an approximately 50% prevalence rate in patients with CKD undergoing conventional dialysis (3 times a week, 4 h per session) [19], the sample size was calculated as 57 patients, with an *α* = 0.05 and *β* = 90% (test power).

The Kolmogorov–Smirnov normality test will first be performed to determine whether a normal distribution sample is present. A descriptive analysis will be performed, with the data expressed as either mean and standard deviation or median values and 95% confidence intervals, as appropriate. One-way analysis of variance will be used for comparisons between work shifts once the samples have a normal distribution. V_0.2_ and ΔV (%) values will be linearly correlated with the AHI, for which either the Pearson or Spearman correlation test will be used, depending on the sample distribution. Either the non-paired Student *t* test or Mann–Whitney test will be used for comparisons between individuals with and those without OSA.

In addition, a logistic regression analysis of continuous factors with categorical responses will be performed. Receiver operating characteristic (ROC) curves will be constructed to determine the sensitivity (true-positive rate) versus 100% specificity (false-positive rate) at various levels of the measured $\Delta \dot{V}$ (%) and V_0.2_ (%) to identify the cut-off value yielding the largest number of correctly classified patients. The statistical analysis will be performed by an experienced statistician using the JMP version 8.0 (SAS/STAT® Software, SAS Institute Inc., Cary, NC, USA) and SPSS version 16.0 programs (Somers NY). A 5% level of significance and 95% confidence interval will be applied.

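### Background β-blocker use is held constant within patients but is neither listed for recording nor named as a covariate, so the group comparison of heart rate variability loses precision and, where groups are not exchangeable, could read a prescribing difference as a group effect

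*Protocol article*

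**What the plan says.** All references are to the protocol article.

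- **Haemodialysis (Study interventions).** The rule is that "during the trial, the patients were not permitted to change their medication or start new drugs, especially antiplatelet agents", followed by "angiotensin-converting enzyme inhibitors, angiotensin II receptor antagonists, calcium-channel blockers, and β-blockers". Those who needed a change left the study: "The patients who required a change in medication for medical reasons were subsequently excluded from the study". The one substance barred outright is N-acetylcysteine, which "was also prohibited in view of its potential influence on ischemia-reperfusion injury".
- **Subjects.** The exclusion criteria ("craniofacial abnormalities; undergoing active treatment of sleep apnea; active malignancy; active alcohol and/or drug abuse", and dementia or refractory psychiatric disease) name no cardiovascular drug. Ongoing use is therefore allowed.
- **Clinical evaluation.** Chart data are itemised down to single laboratory values and end with "duration of dialysis therapy, comorbidities, and aetiology of kidney disease". Medication is not listed.
- **Aims and hypotheses.** Objective 2 is "to determine the behaviour of sympathetic and parasympathetic autonomic nervous system activity through an analysis of heart rate variability". Heart rate and blood pressure are also measured.
- **Sample size calculation and statistical analysis.** "One-way analysis of variance will be used for comparisons between work shifts once the samples have a normal distribution". I read the shifts as the dialysis shifts, because the Discussion speaks of different haemodialysis shifts. Patients with and without obstructive sleep apnea (OSA) are compared by Student t or Mann–Whitney test. A logistic regression is announced, but its factors are not named.
- **Randomization.** Three groups are said to be formed by randomization: diurnal haemodialysis, nocturnal haemodialysis, and CKD without dialysis. No allocation ratio is given.

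**The concern.** The article singles out β-blockers as needing control, then controls them only in the way that serves a within-patient comparison. The negative expiratory pressure test before and after a session is well served by this. The comparison of groups is not: a patient on a β-blocker stays on it and one without stays without, so any difference in use between groups remains throughout.

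This matters most for objective 2, whose only measure is heart rate variability (HRV). That β-blockers act on heart rate and its variability is general pharmacology and is not stated in the article. If it is granted, drug use adds variance to the HRV comparison, and an uneven split moves the group difference. An analysis plan can adjust only for what was collected, so the list of chart data is where the matter has to be settled.

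**Working it through.** **Inputs.** From the article: 57 patients, three groups, one-way ANOVA without a named covariate. Assumed, because the article gives no figure: β-blocker use *p* = 30–50%; difference between users and non-users *d* = 0.5–1.0 SD, with SD taken among patients of the same drug status; 19 per arm (57/3) or 57 per arm.

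**Why both arm sizes.** The article does not say whether 57 is a total or a number per group, and recalculation does not settle it. For 16.9% against 50%, two-sided α = 0.05, 90% power and equal arms, the mean proportion is 0.3345 and

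n = [1.96 × √(2 × 0.3345 × 0.6655) + 1.2816 × √(0.169 × 0.831 + 0.5 × 0.5)]² / 0.331² = (1.308 + 0.801)² / 0.1096 = 40.6, so 41 per arm or 82 in two arms.

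Power is about 77% with 57 in two equal arms and 97% with 57 per arm. Neither matches 90%, so both readings are carried below.

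**Step 1: chance imbalance under true randomization.** For two independent binomial counts, the exact probability that a given pair of arms differs by at least 21 percentage points (4/19 = 12/57 = 21.1 points):

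| Per arm | p = 30% | p = 50% |
|---|---|---|
| 19 | 21.4% | 25.6% |
| 57 | 1.8% | 3.1% |

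A gap of at least 5/19 (26 points) with 19 per arm has probability 11.0% to 14.3%.

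**Step 2: what such a gap does.** Shift in the group difference = d × gap. For a 5/19 gap: 0.5 × 0.263 = 0.13 SD, 0.8 × 0.263 = 0.21 SD, 1.0 × 0.263 = 0.26 SD. The standard error of a 19 v 19 difference is at least √(2/19) = 0.32 SD, so the shift is smaller than one standard error.

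**Step 3: error rate of the unadjusted ANOVA.** Simulated with three groups, no dialysis effect and d = 0.5–0.8:

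| Drug use in the three groups | 19 per group | 57 per group |
|---|---|---|
| 40/40/40% (as randomization gives) | 5.1–5.2% | 5.0–5.2% |
| 30/50/50% (systematic) | 5.7–6.8% | 7.6–12.1% |
| 20/60/60% (systematic) | 8.4–14.2% | 17.0–35.6% |

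With equal expected use the test is valid. Only systematic inequality raises the error rate, and a larger sample then makes it worse.

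**Step 4: what adjustment gains.** Share of variance removed = p(1 − p)d² / [1 + p(1 − p)d²].

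- p = 30%: 0.0525/1.0525 = 5% at d = 0.5; 0.21/1.21 = 17% at d = 1.0.
- p = 50%: 0.0625/1.0625 = 6% at d = 0.5; 0.25/1.25 = 20% at d = 1.0.

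**Step 5: where systematic inequality could arise.** Patients with and without OSA are never randomized to that status, so randomization of the dialysis groups does not protect that comparison. For the control group, Subjects requires an indication for dialysis, while Randomization describes controls who are not dialysed. Clinical evaluation also takes the duration of dialysis therapy from the charts, which suggests that some patients are already on dialysis at entry. These passages must be reconciled before the control can be taken as exchangeable with the dialysed groups.

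**The case against.** The strongest reply is that the groups are stated to be randomized. Prescribing then differs only by chance, the unadjusted ANOVA already allows for that, and Step 3 confirms an error rate near 5%. This stands. A reader might infer that unequal drug use will show up as an effect of the dialysis group. The document does not support that for the design as stated: the 0.13–0.26 SD in Step 2 is a chance shift, not a bias.

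Second, this is a condensed article. A reader might infer that medication is never recorded or never adjusted for. That also goes too far. The freeze cannot be run without knowing each patient's drugs, the factors of the logistic regression are not given, and an unseen plan may name covariates. What can be said is that medication is not listed where chart data are itemised, and is not named as a covariate where the tests are stated.

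Third, the figures depend on assumptions. If 57 is the number per arm, marked chance imbalance is rare.

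Fourth, one might want to adjust the depression, anxiety, sleepiness and polysomnography results for hypnotics or antidepressants too. The article does not mention these drugs, and their use may reflect the very outcome being measured, so adjustment could remove real differences. That step is not supported.

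The objection does not reach the OSA comparison, the doubtful control group, or the precision available from a covariate.

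The removal of patients whose medication changed after entry is a separate matter, and this point does not rest on it.

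**Conclusion.** The point holds in a limited form. The medication rule stabilises β-blocker use within patients and does nothing to balance it between groups, and the listed data and stated tests do not make up for this. Under true randomization the consequence is lost precision (about 5–20% of the HRV variance for d = 0.5–1.0 SD and 30–50% use) and chance imbalance, which is common with 19 per arm and uncommon with 57. The type I error is not inflated.

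Bias is a possibility, confined to the OSA comparison and to the non-dialysed control if that group is not exchangeable. There a prescribing difference could read as a group difference. On the assumed 20/60/60% pattern, the error rate at 19 per group would be 8–14%. Prevalence, drug effect and arm size are assumptions, and the action of the drug is outside knowledge. This is an inexpensive improvement, not a flaw that invalidates the comparison.

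**What to change.** 1. Add baseline β-blocker use (yes/no) to the chart data listed under Clinical evaluation.
2. Tabulate it by randomized group, and for patients with and without OSA.
3. In the between-group comparisons of HRV and heart rate, replace one-way ANOVA with a pre-specified ANCOVA or linear model that has group and β-blocker use as terms. Where HRV or heart rate is compared by OSA status, use the same model with OSA status in place of group.
4. Repeat the HRV comparison in non-users as supportive only. At 30–50% use and 19 per arm it would rest on about 10 to 13 patients per arm (19 × 0.5 = 9.5; 19 × 0.7 = 13.3).
5. Leave the depression, anxiety, sleepiness and polysomnography comparisons unadjusted for sleep- or mood-active drugs.

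The cost is one field from charts already being read and one degree of freedom. No patient's treatment changes. Adjustment does not repair a control group that was not truly randomized; that conflict has to be resolved in its own right.
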